### Harms

In this study, any adverse event (AE) that meets the following criteria will be recorded:

AEs that meet a grading severity of 3 or more as per the Common Terminology Criteria for Adverse Events (CTCAE) V5.AEs assessed as possibly or related either directly or indirectly to the trial intervention or trial procedures.

AEs that, in the opinion of the study team or participant, are considered reportable

A serious AE (SAE) is any untoward medical occurrence that at any administration level:

Results in death.Is life-threatening.Life-threatening in the definition of serious refers to an event in which the participant was at risk of death at the time of the event, it does not refer to an event which hypothetically might have caused death if it were more severe.Requires inpatient hospitalisation or prolongation of existing hospitalisation.Results in persistent or significant disability/incapacity.Is a congenital anomaly/birth defect.Is an important medical event that, although not immediately life-threatening or resulting in death or hospitalisation, based on appropriate medical and scientific judgement, may jeopardise the participant and/or require intervention to prevent one of the outcomes listed above.

AEs occurring after screening but prior to baseline will be recorded as medical history, unless possibly related to a study procedure, in which case they will be reported as an AE. AEs will be tracked until the AE resolves, stabilises or the subject is lost to follow-up.

AE and SAE data may be derived from a number of sources including the research assessment, interaction with study clinical team or reported to the study team by the treating service.

Any SAE occurring during the study, irrespective of the treatment received by the participant, must be reported to the sponsor within 24 hours of the investigator or designee becoming aware of the SAE regardless of the relationship to the intervention. SAEs which are expected to be due to the participant’s underlying illness are not required to be reported in an expedited manner. These events are still required to be recorded for participant safety, data recording and tracking purposes. The investigator should always provide an assessment of causality at the time of the initial report. A follow-up report should be completed when outstanding information becomes available, when there is a significant change in the event or when the event resolves. SAEs will be reported to the governing Human Research Ethics Committee (HREC) in accordance with HREC requirements.

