#### Human support

The *Momentum* platform is moderated by clinicians, peer workers and career consultants. *Momentum* moderators work together as a multidisciplinary team, meeting fortnightly as a whole team to review engagement on the platform and discuss engagement strategies (often influenced by SDT). Moderators can also communicate with one another via chat messaging and discipline-specific activity logs on *Momentum*. The moderation team is led by the trial moderation coordinator who is also a clinician. Each discipline has a specific moderation manual that guides processes during the trial intervention period (available on request).

*Clinicians*: each young person on *Momentum* receives support from a mental health clinician (eg, clinical psychologist, social worker) with experience working with young people. The clinician is a supportive and trusted expert, providing support in line with the supportive accountability model.^58^ Contacts may be synchronous (ie, phone or video calls) or asynchronous (ie, SMS/chat message). *Momentum* clinicians also ensure clinical safety on the platform by monitoring the clinical status of young people in their caseload (through all synchronous and asynchronous contact and reviewing research measures) and conducting safety checks two times per day of all written text by young people on the platform.

Clinicians welcome their allocated young people to the platform via an initial ‘welcome call’, during which they provide a platform orientation, support the young person to set goals for their time on the platform (eg, how often to complete content) and develop a formulation. The platform orientation is typically performed via video call, while all other synchronous interactions are via phone unless offering a video call may assist in boosting engagement with the platform. The formulation then informs SDT-informed support provided (appropriately balancing autonomy, competence and relatedness) and the selection and tailoring of the therapy journey. Clinicians aim to maintain weekly contact with the young person across the 12-month intervention period.

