Clinical risk is managed through both manual and automated procedures. First, clinical moderators monitor the system twice daily on weekdays and once daily on weekends for evidence of clinical risk or deterioration. Any detected increased risk activates the *Momentum* risk and safety protocol, which includes one or more of the following: a risk assessment with the young person, informing the research team, alerting the emergency contact nominated by the participant and liaising with suitable emergency services where necessary. In addition, the system incorporates visible emergency guidelines and contact information. Finally, *Momentum* includes an automated keyword detection function, which activates each time a participant posts a contribution indicative of clinical risk, or a post containing potentially offensive words. The function blocks posts with notifications sent to the young person and the moderator, who can ‘unblock’ the post should they determine it unproblematic.

If, while in contact with a young person, the clinical moderator becomes aware of a clinically significant deterioration of symptoms, increased risk of suicide or a hospital admission, the clinician performs an assessment to determine the risks and benefits of a temporary withdrawal from *Momentum*. Based on this assessment, and in consultation with the young person, the clinical moderation team determines whether their account is temporarily suspended, or their level of access is restricted. Following suspensions or restrictions to a user’s account, the clinician will contact the young person at monthly intervals to ascertain whether the account is to be reactivated.

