### Participant timeline

Following informed consent, participants are enrolled in the trial and screened for eligibility. Once eligibility is established, participants complete the baseline assessment within a 1 month window. Participants are randomised after the completion of baseline measures. Participants in the intervention group receive access to *Momentum* after randomisation for the duration of the study period. All participants complete follow-up assessments at 4 months, 8 months and 12 months, respectively.

The participant timeline is outlined in table 3.

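### Pooled adverse event counts by arm are open to detection bias, because one of the three event sources exists in practice only in the Momentum arm

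*Protocol article*

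**What the plan says.** The Harms section of the protocol article names the sources of AE and SAE data: "AE and SAE data may be derived from a number of sources including the research assessment, interaction with study clinical team". The same sentence ends by naming the treating service as a third route. It sets no rule for separating them.

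Human support describes the clinicians attached to the platform: "Clinicians aim to maintain weekly contact with the young person across the 12-month intervention period". They also monitor clinical status by "conducting safety checks two times per day of all written text by young people on the platform". Safety protocol gives a slightly different frequency: "clinical moderators monitor the system twice daily on weekdays and once daily on weekends for evidence of clinical risk or deterioration". When risk is detected, one of the possible responses is "informing the research team".

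Contact by the research team is the same in both arms. Participant timeline says: "All participants complete follow-up assessments at 4 months, 8 months and 12 months, respectively". Table 3 schedules the C-SSRS (suicidality), the abbreviated CAARMS (transition to psychosis) and the RUQ at each of these points, and Statistical methods confirms that the RUQ covers hospitalisations.

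An event is recorded if it meets any one of three criteria in Harms: CTCAE grade 3 or above; relatedness, worded as "AEs assessed as possibly or related either directly or indirectly to the trial intervention or trial procedures"; or the view of the study team or participant that it should be reported. SAEs must be reported whichever treatment the participant received, with the clock starting when the investigator or a designee becomes aware.

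**The concern.** Two of the three sources are open to both arms. The remaining one is not, and it is the most frequent of the three. It is also directed at the events that matter for safety: Safety protocol has moderators look for risk and deterioration and act on suicide risk and hospital admission.

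For lower-grade events the recording rule pulls in the same direction. Only Momentum participants can have an event related to the intervention itself. The people who see the additional events, moderators and participants, are unmasked according to the article's list of strengths and limitations.

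If all recorded events are put in one table by arm, an excess in the Momentum column could reflect better detection, a real effect, or both, and the table could not tell them apart. This matters in a population whose underlying illness is expected to produce events over 12 months, and in a trial where a trial management group, in place of a data monitoring committee, considers discontinuation.

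**Working it through.** The article states no AE rate, AE hypothesis or AE test, so there is no figure to reproduce. The check has three steps.

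**1. Which arm each source reaches**

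| Source in Harms | TAU | Momentum + TAU |
|---|---|---|
| Research assessment | 4, 8 and 12 months | 4, 8 and 12 months |
| Study clinical team | no counterpart described | weekly contact as an aim, plus platform checks |
| Treating service | open | open |

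This assumes that the study clinical team means the Momentum clinicians. No other study clinicians in contact with participants after randomisation are described.

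**2. Scheduled opportunities over 12 months (52 weeks)**

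- Both arms: 3 follow-up assessments.
- Momentum only, clinician contact: 52 × 1 = 52 at most.
- Momentum only, platform checks by the Safety protocol schedule: 52 × (5 × 2 + 2 × 1) = 624.
- Momentum only, platform checks by the Human support wording: 52 × 7 × 2 = 728.

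These are chances to notice something and do not count AE enquiries. The text does not say that each check feeds the AE record. The two statements of checking frequency differ at weekends and need to be reconciled, but the present point holds under either.

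**3. What unequal detection would do**

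Let the true proportion of participants with an event be p in both arms, and the share detected be d(TAU) and d(M). The observed risk ratio is p·d(M) / p·d(TAU) = d(M)/d(TAU), so p cancels. Expected counts use 220/2 = 110 per arm and, for illustration, p = 20%, which is 22 true cases per arm. All detection shares and p are assumptions.

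| d(TAU) | d(M) | Observed risk ratio | TAU, of 110 | Momentum, of 110 |
|---|---|---|---|---|
| 90% | 100% | 1.11 | 19.8 | 22.0 |
| 80% | 95% | 1.19 | 17.6 | 20.9 |
| 70% | 95% | 1.36 | 15.4 | 20.9 |
| 50% | 90% | 1.80 | 11.0 | 19.8 |
| 50% | 100% | 2.00 | 11.0 | 22.0 |

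At p = 10% the last row becomes 5.5 versus 11.0, and at p = 30% it becomes 16.5 versus 33.0; the ratio stays at 2.0. Where detection is equal, as it should be for events captured through the common assessments, the ratio is 1.0.

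**The case against.** The strongest reply is that the article already gives both arms a common basis for judging harm. Research assessments and treating-service reports reach TAU participants, who are under service care. The most serious foreseeable harms are measured on an identical schedule by C-SSRS, CAARMS and RUQ, and the research assistants who make the interviewer ratings are meant to be masked. The grade 3 threshold and the SAE rule are the same in both arms. Trial procedures apply to both arms, and a TAU participant can also ask for an event to be reported. No between-arm test of AE counts is stated, and AE form fields and safety table layouts are often left to a fuller protocol.

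Most of this stands, and it limits the point. A reader might infer that harms cannot be compared between the arms at all, or that AEs come only through Momentum contacts. The documents support neither reading: two of the three sources and the three scheduled measures are shared. A reader might also take 52 contacts against 3 assessments as a measure of the bias. It is not one, because weekly contact is an aim and informing the research team is only one of several possible responses to detected risk. Nor does the point undermine the sponsor's low-risk assessment, which does not rest on AE counts by arm.

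The objection does not remove the one-arm source. A shared SAE definition does not equalise awareness, and awareness is what starts the report. The absence of a formal test does not help much either, since any AE table by arm invites the comparison. The concern is also with what Harms states, which is three sources taken together, rather than with a detail left out. The article says under Protocol and statistical analysis plan that the analysis plan is confined to the protocol, so a separate plan cannot be presumed to resolve it.

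**Conclusion.** The point holds in a limited form. Pooled AE counts by arm are open to detection bias, most likely in the direction of overstating harm with Momentum. Lower-grade events are the most exposed, because both detection and the recording criteria differ in practice. SAEs and grade 3 or higher events share one definition and are exposed only through awareness. Suicidality, transition to psychosis and hospitalisation, as collected at the scheduled assessments, remain comparable.

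The size cannot be derived from the document. Under the assumed detection pairs above, with equal true risk, the spurious risk ratio lies between about 1.1 and 2.0. No single value in that range should be read as a prediction. The conclusion rests on reading the study clinical team as the Momentum clinicians; if that team has equivalent contact with TAU participants, the article should say so and the point largely falls away.

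**What to change.** In the Harms section:

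- Record for each AE and SAE every source that reported it, not only the first. An event noticed by a moderator and later reported at an assessment then still counts as found by a common source. Otherwise the comparison would lose Momentum events and tilt the other way.
- Base any between-arm comparison on events found through the common 4-, 8- and 12-month assessments (including C-SSRS, CAARMS and RUQ hospitalisations) and treating-service reports, with one severity threshold applied to both arms.
- List events found only through Momentum clinician contact or platform monitoring separately and descriptively.
- Report all SAEs in full by arm, with their source.

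Safety handling of events is unchanged. The cost is one source field and a reporting rule, with no extra visits. The downside is that the comparative table will omit some real Momentum-arm events; they remain visible in the separate listing.

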### Participant timeline

Following informed consent, participants are enrolled in the trial and screened for eligibility. Once eligibility is established, participants complete the baseline assessment within a 1 month window. Participants are randomised after the completion of baseline measures. Participants in the intervention group receive access to *Momentum* after randomisation for the duration of the study period. All participants complete follow-up assessments at 4 months, 8 months and 12 months, respectively.

The participant timeline is outlined in table 3.

### Sample size

Sample size was determined by power analysis using G*Power 3. The primary outcome is the difference in social functioning at 12 months. Our pilot study found a very large effect size (d=1.83, p<0.001) improvement in social functioning from baseline to 2-month follow-up.^39^ This contrasts with follow-up and treatment studies in UHR patients, where social functioning has not improved over time.^51^ Thus, we conservatively assume a medium treatment effect (Cohen’s *d*=0.45), for which a total sample of 180 participants is required to achieve 85% power (alpha=0.05) or 128 participants to achieve 80% power (Cohen’s *d*=0.5). The same applies to all continuous secondary outcome measures (eg, depression, anxiety, social anxiety, role functioning). A total of 220 young people will be recruited, allowing for an 18% attrition rate following randomisation. This compares favourably with the attrition rates in the *Momentum* pilot (7%).

### Recruitment

Participants will be recruited from primary and specialist youth mental health services. In Victoria, study RAs attend weekly clinical review meetings at PACE and headspace services to identify eligible clients. In NSW, a study clinical liaison is appointed at satellite sites to actively facilitate recruitment at the site. The study liaison attends clinical review meetings, engages with treating clinicians and screens clinical files to identify potentially eligible clients. The study liaison introduces the trial to the client and obtains consent to share contact details with Orygen. Young people can also self-refer via the study recruitment page on the Orygen website.

### Randomisation: sequence generation, allocation concealment mechanism and implementation

The randomisation schedule is generated by a statistician independent of the study, programmed in the RPMS and not accessible by the study team. Participants are randomly assigned to the treatment condition via the RPMS using randomly permutated blocks with a 1:1 allocation ratio. Participants are stratified by age (<18 years and ≥18 years), sex at birth and recruitment site.

Once eligibility is established, participants complete the baseline assessment, after which participants are randomised by the research assistant via a secure online RPMS. The RPMS sends an automated email to the study coordinator and principal investigator, notifying them of the outcome of randomisation. The study coordinator informs each participant of their treatment allocation via SMS.

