### Trial design and setting

The study design is a prospective, parallel-group, rater-masked, superiority RCT with a 1:1 allocation ratio. Approximately 220 participants at UHR for psychosis will be allocated to either TAU or TAU + *Momentum*.

The trial includes a 4-year recruitment period, commencing in November 2019, and a 12-month treatment phase, with the study being completed within 5 years (December 2024). The design comprises four monthly assessment points across 12 months. The protocol development addressed all aspects of Good Clinical Practice,^43^ Consolidated Standards of Reporting Trials EHEALTH criteria^44^ and Standard Protocol Items: Recommendations for Interventional Trials guidelines.^45^

Participant recruitment commenced in October 2019 at services in the North-Western Melbourne (Victoria, Australia) catchment. Specifically, recruitment took place through the Personal Assessment and Crisis Evaluation (PACE) programme, a part of the Orygen Specialist Program and headspace centres led by Orygen (in the Melbourne suburbs of Sunshine and Glenroy). These services support young people who may be at risk of developing psychosis.^46 47^ Orygen is the world’s largest research and knowledge translation organisation focused on early intervention in mental ill-health in young people.

Orygen Digital, the digital mental health division of Orygen and Centre for Youth Mental Health at The University of Melbourne, designs, delivers and evaluates evidence-based digital services for youth mental health. In April 2020, Orygen Digital commenced implementation of the MOST platform across all Victorian youth mental health services both as part of the Victorian State Government’s response to the COVID-19 pandemic and in response to the recommendations of the Royal Commission into Victoria’s Mental Health System.^48^ Due to the overlap between study and implementation sites, participant recruitment from Victorian sites ceased in October 2020. Instead, satellite recruitment sites were established at two services within the South-Eastern Sydney Local Health District (Bondi Junction Community Mental Health Centre and headspace Bondi Junction) and at headspace services in the Illawarra region, New South Wales (NSW), operated by Grand Pacific Health (Wollongong, Nowra).

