#### Other measured outcomes

Additional exploratory outcomes, potential covariates and intervention-only outcomes are outlined in table 3.

**Table 3 T3:** Schedule of enrolment, assessments and intervention

	Enrolment		Post randomisation		
	-t_1_ - 0	0	t1 (4 months)	t2 (8 months)	t3 (12 months)
Informed consent	✓				
Eligibility screen	✓				
Primary outcome and measure					
Social functioning (Global Functioning: Social)	✓		✓	✓	✓
Secondary outcomes and measures					
Depression (QIDS)	✓		✓	✓	✓
Anxiety (GAD-7)	✓		✓	✓	✓
Social anxiety (LSAS)	✓		✓	✓	✓
Role functioning (Global Functioning: Role)	✓		✓	✓	✓
Vocational status (RUQ)	✓		✓	✓	✓
Cost-effectiveness (RUQ and AQoL-8D)	✓		✓	✓	✓
Exploratory outcomes and measures					
Self-efficacy (SES)	✓		✓	✓	✓
Social support (SPS)	✓		✓	✓	✓
Subjective well-being (SWLS)	✓		✓	✓	✓
Transition to psychosis (Abbreviated CAARMS)	✓		✓	✓	✓
Attenuated psychotic symptoms (Abbreviated CAARMS)	✓		✓	✓	✓
Quality of life (AQoL-8D)	✓		✓	✓	✓
Stress (PSS)	✓		✓	✓	✓
Loneliness (UCLA Loneliness Scale^77^)	✓		✓	✓	✓
Self-esteem (Rosenberg SES)	✓		✓	✓	✓
Psychological well-being (BPNS)	✓		✓	✓	✓
Sleep quality (PSQI)	✓		✓	✓	✓
Suicidal ideation and attempts (CSSRS)	✓		✓	✓	✓
Strengths use (SUS)	✓		✓	✓	✓
Mindfulness skills (FMI)	✓		✓	✓	✓
Self-compassion (SCS-SF)	✓		✓	✓	✓
Substance use (ASSIST)*	✓				✓
Anomalous self-experience (IPASE)*	✓				
History of trauma (ACE)*	✓				
Randomisation		✓			
Intervention		Continuous			
Comparator		Continuous			
Digital phenotype (AWARE-Light^78^)		Continuous			
Daily social functioning and subjective well-being (SEMA3 application)		Daily			
Intervention group-only outcomes and measures					
Intervention acceptability (qualitative evaluation via semistructured interview)					✓
Therapeutic alliance (WAI-C, WAI-T)		✓	✓	✓	✓
Usage data		Continuous			

* Potential covariates.

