### Statistical methods

Primary analyses will be undertaken on an intention-to-treat basis. Mixed-model repeated measures (MMRM) analyses, including random intercepts to account for individual variability in baseline levels of social functioning, will be used to compare change in social functioning between the two treatment groups over the 12-month follow-up. MMRM is the analysis of choice because assumptions of traditional data analysis methods (eg, Analyis of Variance (ANOVA), logistic regression) may be violated, such as the assumption of homogeneity of regression across time points.^70^ Time (baseline, 4 months, 8 months and 12 months) will be the within-subjects factor and group (*Momentum* vs TAU) the between-subjects factor. Random intercepts account for individual differences in baseline levels of the outcome (eg, social functioning at the start of the study). However, individuals may also differ in how their outcomes change over time (eg, the rate or direction of improvement/decline in social functioning). Random slopes model this variability by allowing each participant to have their own trajectory (slope) over time. We will test whether including random slopes significantly improves model fit, but if the variance of slopes is negligible, a simpler model with only random intercepts will be adopted. MMRM will also be used to analyse change in the continuous secondary and exploratory outcomes over 12 months. Group differences in risk of transition to psychosis and vocational outcome will be tested using Fisher’s exact test, an alternative to the χ^2^ test more robust to small sample sizes.^71^ Time to transition to psychosis will be assessed by survival analysis (using either proportional hazard or accelerated life-time models).

Exploratory mechanisms of action (self-efficacy, social support and subjective well-being) analyses will be conducted using a multilevel structural equation modelling framework to assess mediation.^72^ Specifically, person-specific slopes representing change over time in the proposed mechanism-of-action variables (eg, self-efficacy) will be tested as mediators of the effect of treatment group (*Momentum* vs TAU) on social functioning.

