### Protocol and statistical analysis plan

The protocol will be available via the trial registry (ANZCTR). The statistical analysis plan is limited to the protocol.

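### Randomisation is stratified by age group, sex at birth and site, but the stated model includes none of them: a mild, conservative loss that depends on the contrast and is cheap to avoid

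*Protocol article*

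**What the plan says.** The randomisation section assigns participants "using randomly permutated blocks with a 1:1 allocation ratio" and continues: "Participants are stratified by age (<18 years and ≥18 years), sex at birth and recruitment site". The abstract repeats this.

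Statistical methods then sets out the primary model: "Time (baseline, 4 months, 8 months and 12 months) will be the within-subjects factor and group (*Momentum* vs TAU) the between-subjects factor". The random effects are described as "including random intercepts to account for individual variability in baseline levels of social functioning", with random slopes added if they improve fit. Both are per participant and represent neither site nor any other stratum. The same type of model serves the continuous secondary and exploratory outcomes.

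Age group, sex and site appear in no model in the article. Other measured outcomes does announce "Additional exploratory outcomes, potential covariates and intervention-only outcomes are outlined in table 3", but the three measures so marked in Table 3 (ASSIST, IPASE and ACE) are not stratification factors. The last section says "The statistical analysis plan is limited to the protocol".

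Trial design and setting bears on site: "Due to the overlap between study and implementation sites, participant recruitment from Victorian sites ceased in October 2020". Recruitment then moved to services in New South Wales.

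**The concern.** Balancing the arms within strata removes the strata's share of variance from the treatment comparison. A model that omits the strata leaves that share in its error term. Its standard error is then larger than the true sampling variation, the test runs below its nominal level and some power is lost. Chance imbalance left by incomplete blocks also goes uncorrected.

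Site is the factor most worth considering. It carries state, service type (a specialist programme for young people at ultra-high risk, a community mental health centre, or headspace) and calendar period, because the Victorian services stopped recruiting in October 2020.

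**Working it through.** **The plan's own figure.** Inputs from Sample size: d = 0.45, alpha 0.05, 85% power, 180 evaluable, 18% attrition, 220 recruited; alternatively d = 0.5, 80% power, 128. A two-sided, two-sample t test (noncentral t) gives 85.1% power with 90 per arm and 80.1% with 64 per arm, so 180 and 128 reproduce. 220 × 0.82 = 180.4, so 220 reproduces too. The calculation used no covariates, so the present point does not alter it.

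**Contrast A: difference at 12 months, as in Sample size.** Let R² be the share of 12-month variance explained by the strata. The documents do not give it; 5%, 10% and 15% are assumed. Take unit variance, 90 per arm and exact balance.

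- Standard error reported without strata: √(2/90) = 0.1491.
- True standard error, which the model with strata would report: √((1 − R²) × 2/90).
- False-positive rate without strata: 2 × [1 − Φ(1.96/√(1 − R²))].
- Power without strata: Φ[(0.45 − 1.96 × 0.1491)/true SE].
- Power with strata: Φ[0.45/true SE − 1.96].

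| R² (assumed) | True SE | Reported SE / true SE | False-positive rate without strata | Power without strata | Power with strata | Gain (points) |
|---|---|---|---|---|---|---|
| 5% | 0.1453 | 1.026 | 4.4% | 86.1% | 87.2% | 1.1 |
| 10% | 0.1414 | 1.054 | 3.9% | 86.8% | 88.9% | 2.1 |
| 15% | 0.1374 | 1.085 | 3.4% | 87.5% | 90.6% | 3.1 |

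Using the noncentral t lowers the power with strata by 0.3 points (86.9%, 88.6%, 90.3%).

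Exact balance is the extreme case. Trial design and setting names seven services. If each is a stratum (an assumption), there are 2 × 2 × 7 = 28 cells of about 220/28 = 7.9 participants. A simulation with 28 strata, blocks of four, 220 randomised and 180 retained (6,000 runs, Monte Carlo error about 0.3 points) gave false-positive rates of 4.7%, 4.6% and 3.7% at R² = 5%, 10% and 15%. These are nearer 5% than the table.

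**Contrast B: change, with baseline as a level of time, as in Statistical methods.**

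1. *Strata affect level only.* A constant stratum effect is present at baseline and at 12 months, and cancels. The same simulation gave false-positive rates of 5.2%, 5.1% and 4.8%. In fitted random-intercept models with strata explaining 10% of variance, the group-by-12-month standard error was 0.1487 both without and with strata main effects. At 20% it was 0.1499 both ways.
2. *Strata also predict change.* In a simulation with 180 participants where strata explained 10% or 20% of the variance of change, the unadjusted false-positive rate was 3.7% or 3.0%. Power was 82.5% unadjusted against 84.1% adjusted at 10%, and 80.3% against 86.1% at 20%. Each power figure rests on 1,500 runs (Monte Carlo error about 1 point).
3. *Main effects do not repair case 2.* With strata explaining 10% of the variance of change, the fitted group-by-12-month standard error was 0.1527 with and without strata main effects. Only factor-by-visit terms change it.

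**The case against.** The strongest reply is that the table describes a contrast other than the one in the analysis section. That section compares change with baseline as a response, and there stable age, sex and site effects cancel. This stands. The table applies to the 12-month difference named in Sample size; under Statistical methods any loss is conditional on the strata predicting change.

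Secondly, exact balance overstates the shortfall from 5% when strata are small and participants drop out. This stands too, so the tabulated false-positive rates are a lower bound.

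Thirdly, the article names the model's factors without saying that nothing else enters. It refers to a protocol on the registry, its abstract mentions an analysis plan as supplementary material, and neither is shown. This lowers confidence but does not dispose of the point. The article lists the model's terms, leaves the strata out, and says the analysis plan is confined to the protocol.

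A reader might infer that the trial is underpowered or its test invalid. The documents do not support that. Under contrast A, power without strata stays above 85% in every scenario. The figures below 85% in case 2 arise because the simulation added stratum variance on top of the planned unit variance, so they do not show that 180 is too few. A reader might also take it as established that site affects outcome. The documents give no outcome figures by site; that is a plausible inference from the recruitment history only.

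**Conclusion.** The mismatch between design and stated model is real, and its consequence is modest. For a 12-month difference, with strata explaining an assumed 5% to 15% of variance, the false-positive rate is at lowest about 4.4% to 3.4%, closer to 5% in realistic conditions, and about 1 to 3 points of power are lost. For the change contrast there is no loss if the strata affect only the level of functioning, and some loss if they predict change. In every case the error is conservative: no bias in the estimate, no inflation of false positives, and no effect on the 180 and 220. The sizes rest on assumed R² values and, in the simulations, on an assumed count of seven sites. This is a worthwhile improvement to a stated model and not a threat to the trial's validity.

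**What to change.** State in Statistical methods that age group, sex at birth and recruitment site enter the primary and continuous secondary models as fixed effects, with small sites pooled by a prespecified rule, for example by state and service type. Tie the form to the handling of baseline: main effects if baseline is a covariate; factor-by-visit terms if baseline stays a response, since main effects alone leave the change contrast untouched.

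The data are already in the randomisation system and no extra participants are needed. The cost is extra parameters. With seven sites (assumed) the factors use 1 + 1 + 6 = 8 degrees of freedom, or 8 × 4 = 32 parameters over four visits. Pooling to four state-by-service groups would reduce this to (1 + 1 + 3) × 4 = 20. If the strata do not predict change, adjustment costs a little precision: in the simulation with all 28 cells fitted, the standard error of change rose from 0.1490 to 0.1508, about 1%. Fixing the terms and the pooling rule in advance also removes a later choice of covariates.
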